### Cost analysis

Unit costing of distinct health care resources will be in accordance with national guidelines [26]. Cost data will be derived as the product sum of health care volume data and their respective unit cost. Observed health utilities based on the EQ-5D health status profiles will be linked to the lengths of the periods in between measurements to derive QALYs. Incremental cost-effectiveness and cost-utility analyses will be performed to calculate the extra cost per additional ‘responder’ and the extra costs per additional quality adjusted life year respectively. Differences between groups will be assessed by calculating 95 % confidence intervals for the mean differences after non-parametric bootstrapping, drawing at least 1,000 samples of the same size as the original sample separately for each group and with replacement. A cost-effectiveness acceptability curve will be drawn to show the probability of intravenous iron supplementation being cost- effective at willingness-to-pay values up to €80,000 per QALY. Single and multi-way sensitivity analyses will be performed to study the robustness of these findings to plausible changes in key unit costs and to alternative health utility scoring algorithms [27]. With a time horizon of six months of follow-up, no discounting of efficacy and cost data will be applied to account for time preference.

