### Study design

The study is designed as a multicentre randomized clinical trial comparing ferric(III)carboxymaltose infusion with oral supplementation of ferrofumarate in the treatment of preoperative anaemia in colorectal cancer patients. Patients with a proven iron deficiency anaemia who undergo segmental colonic resection or (low) anterior resection because of M0-stage colorectal carcinoma are eligible for inclusion. Patients undergoing local excision of a rectal carcinoma (TEM/EMR/ESR) will not be included. In Fig. 1 you can find the flowchart of the FIT-trial.

When a patient has got a proven iron deficiency anaemia and the patient does not meet the criteria for exclusion, he/she will be included in the trial. Written informed consent will be obtained from each patient. The patients’ albumin and C-reactive protein (CRP) levels are used to derive a Glasgow Prognostic Score (GPS) which can be used as a predictor of post-operative outcome.

Patients will be computer randomized in random blocks of sizes 2 or 4 for either intravenous- or oral iron. Randomization will be stratified for age, colon or rectal carcinoma, open or laparoscopic operation and baseline Hb (8–10 g/dl vs 10–13 g/dl).

Apart from routine 5 year oncological follow-up, patients will be followed more intensively until 6 months after surgery as part of this trial. Hb, transferrin saturation (TSAT), ferritin, Hematocrit and CRP levels are measured at postoperative day 1, day 7, at 4, 8 and 12 weeks to monitor the anaemia.The follow-up schedule is detailed in Fig. 2.

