### Sample size calculation

The principal analysis will be an intention-to-treat comparison of the proportions of patients with iron deficiency anaemia between the two study groups. The trial is designed as a superiority trial, hypothesizing a greater percentage of patients achieving normalization of Hb-level (called ‘responder’) in favour of infusion of ferric(III)carboxymaltose compared to oral iron suppletion. Our power calculation is based on the study of Seid et al. [24], which compared ferric(III)carboxymaltose with oral ferrous sulphate in a population of post-partum women with an iron deficiency anaemia. The proportion achieving a normalization of Hb after two weeks of treatment was 55 % in the intravenous iron group and 35 % in the oral iron group. We expect that the efficacy of the iron therapy is lower in patients with a colorectal carcinoma. Therefore, the expected percentage of patients who achieve normalization of Hb-level (Hb >7.5 mmol/l (12 g/dl) for women and Hb >8.0 mmol/l (13 g/dl) for men) is 45 % in the intravenous iron group and 25 % in the oral iron group. Based on these proportions, a sample size of 89 patients per group is needed for a Chi square test to achieve 80 % power at a two sided alpha of 0.05. With an estimated loss to follow up of 10 %, a sample size of 198 is calculated. We used nQuery advisor version 7.0 to calculate the sample size.

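### The cost and QALY bootstrap ignores the randomisation strata, so its 95% intervals will be somewhat conservative to the extent that those strata predict cost or QALYs

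*Protocol article*

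**What the plan says.** The Study design section of the protocol article describes blocked, stratified allocation: "Patients will be computer randomized in random blocks of sizes 2 or 4 for either intravenous- or oral iron" and "Randomization will be stratified for age, colon or rectal carcinoma, open or laparoscopic operation and baseline Hb", with baseline Hb split at 10 g/dl.

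The Cost analysis section sets out the economic inference: "Differences between groups will be assessed by calculating 95 % confidence intervals for the mean differences after non-parametric bootstrapping", by "drawing at least 1,000 samples of the same size as the original sample separately for each group and with replacement". An acceptability curve follows. That section mentions neither the stratification factors nor any covariate adjustment.

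The Data-analysis section allows analysis of covariance for continuous secondary endpoints. The Cost analysis section does not carry this over to the bootstrap. It gives no standard deviation, expected width or stratum effect for costs or QALYs.

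**The concern.** Stratified blocks make the two arms nearly alike in the stratification factors. The observed difference in mean cost already benefits from that balance. The planned interval does not, because each draw picks patients freely within an arm. The numbers of open operations, rectal tumours or low-Hb patients per arm then vary from draw to draw in a way that the design largely prevents. If those factors are related to cost or QALYs, this added variation enters the interval. It also enters the acceptability curve if the same draws are used, and pulls its probabilities towards one half.

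Cost-effectiveness is a named secondary aim, while the trial is sized for the Hb endpoint only. Precision on the economic side is therefore not planned for, and it makes sense to report what the randomisation has already secured.

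**Working it through.** **Inputs from the article.** Blocks of 2 or 4; four stratification factors; arm-wise bootstrap of mean differences; 198 patients in total.

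**Inputs assumed.** R², the share of outcome variance explained by the strata; each factor binary, giving 2 × 2 × 2 × 2 = 16 strata (no age cut is given); and the factor prevalences used in the simulations.

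**1. The plan's own figure.** The expected response "is 45 % in the intravenous iron group and 25 % in the oral iron group". With pooled variance and no continuity correction:

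n = [1.960 × sqrt(2 × 0.35 × 0.65) + 0.842 × sqrt(0.45 × 0.55 + 0.25 × 0.75)]² / 0.20² = 88.1, rounded up to 89 per group (power 80.4%).

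Allowing for 10% loss, 89/0.90 = 98.9, so 99 per group and 198 in total. The sample size reproduces. It gives the trial size but otherwise has no bearing on this point.

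**2. Large-sample size of the effect.** Let σ² be the outcome variance.
- The arm-wise bootstrap estimates the variance of the difference as σ²(1/n₁ + 1/n₀).
- With strata balanced by design, the true variance is about (1 - R²)σ²(1/n₁ + 1/n₀).
- Width ratio = 1/sqrt(1 - R²).
- Coverage of the nominal 95% interval = 2Φ(1.96/sqrt(1 - R²)) - 1.

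| Assumed R² | Width ratio | Coverage |
|---|---|---|
| 0% | 1.00 | 95.0% |
| 2% | 1.01 | 95.2% |
| 5% | 1.03 | 95.6% |
| 10% | 1.05 | 96.1% |
| 20% | 1.12 | 97.2% |
| 30% | 1.20 | 98.1% |

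**3. Check at the trial's size.** Simulation with 198 patients, blocks of 2 or 4, 4 or 16 strata, normal outcomes and 4,000 runs. The arm-only bootstrap SE divided by the true SE was:
- R² 0%: 0.98-1.01
- R² 5%: 1.01-1.04
- R² 10%: 1.03-1.06
- R² 20%: 1.10-1.11

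Coverage was about 95-97%. The simulation error of each ratio is roughly 1/sqrt(2 × 4,000) = 1.1 percentage points, so this agrees with the formula. One run with skewed outcomes (R² 10%, 16 strata) gave a ratio of 1.015.

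**4. Check of possible remedies.**
- *Resampling within every arm-by-stratum cell.* With 16 strata there are about 198/(16 × 2) = 6.2 patients per cell, and coverage fell to 92.3-93.5%. With 4 strata it was 94.1-94.8%.
- *Regression on the factors.* In a separate simulation (178 patients, 16 strata, log-normal costs, large-sample SEs, 6,000 runs), adjusted intervals covered 94.1-94.6%. The planned intervals were 3%, 7% and 15% wider than the adjusted ones at R² of 3%, 11% and 22%. Part of that gap arises because the adjusted intervals run slightly narrow.

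**5. Is R² = 0 plausible for cost?** The article gives no figure, but its text points away from zero:
- In Table 1 the cumulative intravenous dose differs by 500 mg across Hb 10 g/dl in both weight bands (1500 against 1000 mg; 2000 against 1500 mg). That is the same cut as the Hb stratum.
- The Background links laparoscopic surgery to limited blood loss and rare transfusion, and preoperative anaemia to morbidity.
- The Discussion reports less morbidity in mild to moderate than in more severe anaemia.
- Operative approach cannot affect an Hb measured before the operation, so stratifying on it mainly serves postoperative outcomes.

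**The case against.** The strongest reply is that nothing here is wrong. Arm-wise bootstrapping gives a valid interval that errs on the safe side, the size of the error is unknown, and a journal article may leave adjustment to a fuller economic plan. Much of this stands. The article does not rule out adjustment, and the point is an improvement rather than the correction of an error. It is still more than missing detail, because the article states the resampling scheme and the quantity estimated, and neither uses the strata.

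Three stronger readings are tempting but unsupported.

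- **That the intervals are too wide without qualification.** At R² = 0 they are correct, and the article gives no association between any stratum and cost or QALYs. For QALYs in particular there is no direct evidence, and no QALY-specific simulation was done; only the general formula applies.
- **That the excess is large.** An excess of 15% needs R² = 1 - 1/1.15² = 24%, and 20% needs 1 - 1/1.20² = 31%. Nothing in the article supports values that high. The societal perspective and six-month horizon bring in costs well beyond the surgical admission, which may dilute the influence of operation type and tumour site.
- **That the floor of 1,000 draws is a defect.** The wording sets a minimum, so 10,000 draws already comply. This is not part of the point.

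The remedy is not free of risk either: adjusted intervals can fall slightly below nominal coverage.

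**Conclusion.** The point holds conditionally. The planned bootstrap ignores four factors on which allocation was balanced. Its intervals, and an acceptability curve drawn from the same resamples, will be conservative to the extent that those factors predict cost or QALYs. The excess width is nil at R² = 0, about 1-5% for R² up to 10%, and about 10-12% at 20%.

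The direction follows from the design and is confirmed by formula and simulation. The size rests on an assumed R² and, in the simulations, on an assumed 16-stratum layout and assumed prevalences. For cost, an R² of exactly zero is implausible on the article's own account; for QALYs the question is open. The consequence is some unreported precision on a secondary aim. The primary analysis is unaffected. This is a modest improvement, worth making because it costs little.

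**What to change.** In the Cost analysis section, keep resampling separately by arm. In each draw, estimate the mean cost and mean QALY differences from a linear model with treatment and the four randomisation factors (age, colon or rectum, open or laparoscopic, baseline Hb) as main effects, using the factor values recorded at randomisation. State that the acceptability curve uses the same draws.

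Do not resample within all full strata: at about six patients per cell, coverage drops to about 92-94%.

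Because adjusted intervals may cover about 94-95% rather than exactly 95%, keep the unadjusted arm-wise bootstrap as a sensitivity analysis.

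The cost is a sentence or two in the economic analysis plan and a few lines of code, fixed before the data are analysed. It needs no new data and no change to trial conduct.

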### Ethics and safety

This trial will be conducted according to the principles of the declaration of Helsinki (Fortaleza, October 2013 ) and in accordance with the Medical Research Involving Human Subjects Act (WMO) and other European guidelines, regulations and acts. Data management, monitoring and reporting of the study will be carried out in accordance with the ICH GCP guidelines. The medical ethical committee of the Academic Medical Centre, Amsterdam, the Netherlands, has approved the study protocol (NL50013.018.14). As this trial concerns the effectiveness of a medication a Data Safety Monitoring Board (DSMB) will be assigned. The DSMB will guard the safety of the included patients, give advice on continuation of the study upon superiority of one of the types of treatment, and will guard the methodological quality of the study.

## Discussion

This is the first randomized controlled trial to determine the efficacy of preoperative iron supplementation in exclusively anaemic patients with a colorectal carcinoma. In current literature there are two randomized trials on preoperative iron supplementation for colorectal carcinoma patients [20, 21]. Both included non-anaemic patients, were small sized and used a fixed dosage of iron supplementation [20]. As iron-therapy is unlikely to be effective when the patient has no deficiency this is a huge confounder in both studies. Apart from these two randomized controlled trials there are four cohort studies addressing preoperative iron supplementation in patients undergoing surgery for colorectal carcinoma [22, 28–30]. These four cohort series all focussed mainly on perioperative blood transfusion rate. Currently, in centralized centres the blood transfusion rate after colorectal surgery is around 4 % [1]. This low blood transfusion rate adds to the debate whether postoperative transfusion is the most important clinical endpoint assessing patients with anaemia.

It is well-known that anaemia is associated with impaired physical performance and lower quality of life [5]. In a retrospective cohort study of 227425 patients undergoing non-cardiac surgery Musallam et al. [13] showed that anaemia is associated with a higher postoperative morbidity. A reduction in morbidity was seen in the non-anaemic patients compared to anaemic patients from 28 % to 5 % in non-anaemic patients. A reduction in postoperative morbidity was also seen even in mild to moderate anaemic patients, compared to more severe anaemic patients. This strengthens our hypothesis that more effective treatment of anaemia improves the morbidity after surgery.

In current practice, the period between diagnosis and surgery is approximately two to three weeks. This provides a window of opportunity for treatment with iron supplementation, as it takes time to increase the Hb-level with iron therapy. Blood transfusions or erythropoietin stimulating agents (ESA) are both successful in the treatment of anaemia, but as these modalities significantly increase the risk of recurrence and even mortality, they should be given with restraint [31]. Both intravenous and oral therapy are currently used and accepted as treatment of iron deficiency anaemia. However, a study directly comparing the effectiveness of both treatment options and simultaneously assessing the correlation with postoperative outcome has never been performed. Therefore the primary aim of this trial is to provide evidence on the safest and most effective treatment option of anaemia in the limited time period of the preoperative setting.

## Abbreviations

FIT: Ferric(III)carboxymaltose infusion with oral iron supplementation in the treatment of preoperative anaemia
GI: Gastro-intestinal
ESA: Erythropoietin stimulating agents
HB: Haemoglobin
TEM: Transanal Endoscopic Microsurgery
ESD: Endoscopic Submucosal Dissection
EMR: Endoscopic Mucosal Resection
ERAS: Enhanced recovery after surgery
QALY: Quality adjusted life years
GPS: Glasgow Prognostic Score
CRP: C-reactive protein
TSAT: Transferrin saturation
SPC: Summary of Product Characteristics
GFR: Glomerular Filtration rate
FAS: Full analysis Set
